## Abstract

**Background:**

Promoting psychological well-being and preventing distress among pregnant women is an important public health goal. In addition to adversely impacting the mother’s health and well-being, psychological distress in pregnancy increases the risk of poor pregnancy outcomes, compromises infant socioemotional development and bonding, and heightens maternal and child vulnerability in the postpartum period. Mindfulness and compassion-based interventions show potential for prevention and early intervention for perinatal distress. As there is an established need for accessible, scalable, flexible, and low-cost interventions, there is increased interest in the delivery of these programs on the web. This project aims to pilot a three-arm randomized controlled trial (RCT) to determine the feasibility of a full-scale RCT comparing 2 web-based interventions (mindfulness vs loving-kindness and compassion) with a web-based active control condition (progressive muscle relaxation).

**Objective:**

The primary objective of this study is to assess the feasibility of an RCT protocol comparing the 3 conditions delivered on the web as a series of instructional materials and brief daily practices over a course of 8 weeks. The second objective is to explore the experiences of women in the different intervention conditions. The third objective is to estimate SD values for the outcome measures to inform the design of an adequately powered trial to determine the comparative efficacy of the different conditions.

**Methods:**

Pregnant women (n=75) participating in a longitudinal birth cohort study (the ORIGINS project) will be recruited to this study from 18 weeks of gestational age. We will assess the acceptability and feasibility of recruitment and retention strategies and the participants’ engagement and adherence to the interventions. We will also assess the experiences of women in each of the 3 intervention conditions by measuring weekly changes in their well-being and engagement with the program and by conducting a qualitative analysis of postprogram interviews.

**Results:**

This project was funded in September 2019 and received ethics approval on July 8, 2020. Enrollment to the study will commence in September 2020. Feasibility of a full-scale RCT will be assessed using ADePT (*a process for decision making after pilot and feasibility trials*) criteria.

**Conclusions:**

If the study is shown to be feasible, results will be used to inform future full-scale RCTs. Evidence for flexible, scalable, and low-cost interventions could inform population health strategies to promote well-being and reduce psychological distress among pregnant women.

**Trial Registration:**

Australian New Zealand Clinical Trials Registry Number 12620000672954p; http://anzctr.org.au/ACTRN12620000672954p.aspx

**International Registered Report Identifier (IRRID):**

PRR1-10.2196/19803

## Introduction

### Background

Maternal mental health in pregnancy is an issue of substantial public health importance [1]. Anxiety and depression are the most common postpartum difficulties experienced by women globally [2], with an average prevalence of 10% to 15%, although rates as high as 64% have been reported in US samples [2]. Psychological distress during pregnancy is associated with adverse impacts for both the mother and child [3-6]. For example, prenatal symptoms of depression and anxiety are associated with impaired fetal growth [7], risk of child emotional and behavioral problems [8-13], and differences in child brain morphology [14]. These findings align with the Developmental Origins of Health and Disease model [15], which posits that the characteristics of the perinatal environment exert lifelong influences on offspring health risk and resilience. Maternal mental health difficulties in pregnancy can also increase the risk of adjustment difficulties in the postnatal period [16,17].

Despite the availability of accessible and effective treatments for mood disorders, approximately half of the women experiencing perinatal distress do not seek help [18-20]. Such findings demonstrate a need for universal mental health promotion efforts that complement targeted treatment programs and span prevention through early intervention. Nonpharmacological approaches to mood management are also preferred by pregnant women because of concerns about the effects of pharmacological interventions on the developing fetus [21]. Furthermore, research on mental health risk and resilience also illustrates the dual benefits of targeting subclinical symptoms of distress and increasing positive mental health and well-being. For example, although a history of psychiatric symptoms predisposes individuals to future psychopathology, positive mental health both supports recovery from distress and protects against poor mental health in the future [22-25]. Studies with pregnant women have found that prenatal positive mental health traits such as positive affect and optimism are protective of postpartum depression [26,27] and birth outcomes such as preterm delivery [28]. A dual approach aligns with two-factor models of mental health, which recognize distress and well-being as 2 distinct but interrelated continua [22,29,30].

### Meditation-Based Interventions

Meditation-based interventions, including mindfulness-based interventions (MBIs) and compassion-based interventions (CBIs), are promising approaches for improving mental health and reducing psychological distress in the perinatal period. There is considerable evidence demonstrating the effectiveness of MBIs in reducing symptoms of psychological distress and promoting positive mental health in community populations [31,32] and clinical and at-risk groups [33,34]. CBIs (used here to denote meditation interventions focused on loving-kindness, self-compassion, and compassion for others) are similar to MBIs in that standardized protocols tend to be delivered over 8 weeks, with meditation practice considered an *active ingredient* in intervention effectiveness [35,36]. However, there are also important differences: although MBIs focus on cultivating nonjudgmental awareness and acceptance of all present-moment experiences [37], CBIs involve the intentional cultivation of positive affective states (eg, love, kindness, compassion, joy) [38].

Although the literature on CBIs is sparse relative to that for MBIs, reviews and meta-analyses also document positive effects of compassion and loving-kindness meditation practices on positive mental health [39] and psychological distress [35,40,41]. More recent work has demonstrated the greater efficacy of CBI protocols over MBI protocols for some outcomes. For example, Le Nguyen et al [42] reported the superior effects of loving-kindness training over mindfulness training for improving telomere length in novice meditators. Furthermore, Trautwein et al [37] demonstrated the differential benefits of different types of meditation training (attention and loving-kindness) on various cognitive and affective outcomes. Although these findings provide the basis for the development of more targeted intervention approaches, it is not clear which of these outcomes is most relevant for promoting mental health and well-being in pregnant women.

### MBIs and CBIs in Pregnancy

Evidence drawn from observational and experimental studies illustrates the potential benefit of MBIs and CBIs in reducing distress and promoting mental health in the perinatal period. For example, longitudinal studies have found significant inverse associations between trait mindfulness during pregnancy and both depressed mood across pregnancy and low birth weight (<10th percentile, after adjusting for gestational age, parity, and sex) [43]. Preliminary evidence also indicates that maternal mindfulness during pregnancy is associated with better behavioral and regulatory outcomes in infants and children [44,45]. However, results from systematic reviews of perinatal MBIs have been variable [46-48]. Although the literature suggests that mindfulness training in the perinatal period reduces perinatal stress and anxiety [48], there is mixed evidence regarding reductions in depression [48]. This is partly linked to heterogeneity in sample types and methodology as well as differences across intervention protocols.

Although initial evidence demonstrates associations among maternal self-compassion, well-being, and adjustment [49-51], there are only very few studies assessing CBIs in the perinatal period. Those that are available have reported encouraging results. For example, a proof-of-concept study compared a 2-week web-based CBI with web-based cognitive behavioral therapy (CBT) for perinatal women and those planning pregnancy (n=123) [52]. Participants in the 2 groups had similar outcomes in terms of affect, self-reassurance, self-criticism, and self-compassion. However, CBI was superior to CBT in terms of reducing symptoms of depression and anxiety. In another study, a 6-session, 3-week loving-kindness and compassion group program was compared with pregnancy yoga and an untreated control group in a sample of pregnant women (n=109) [53]. In this study, participants in the intervention group reported significant improvements in maternal-fetal attachment, mindfulness, and positive emotion relative to the control groups at posttest and follow-up. There are currently no head-to-head studies comparing the efficacy of MBIs and CBIs among pregnant women.

### Web-Based Meditation-Based Interventions

There are a number of potential benefits of delivering MBIs and CBIs via the internet [52,54], such as the capacity to implement across populations, to reach individuals who might struggle to access face-to-face services, the potential to improve cost-efficiencies, and the ability to provide greater flexibility to service users [55]. Meta-analyses have found small-to-moderate effect sizes for web-based and self-guided MBIs in promoting well-being and reducing symptoms of psychological distress [56]. Although there are limited studies of internet-delivered CBIs, 1 RCT of web-based compassion training for self-critical individuals reported moderate-to-large effect sizes for reductions in distress, relative to usual care [57]. However, it is currently unclear whether MBIs and CBIs delivered on the web are a feasible and efficacious means of reducing stress and promoting well-being in the perinatal period [58]. Available evidence for internet-delivered MBIs highlights some issues with intervention feasibility. For example, 1 RCT found evidence that compared with waitlist control, a web-based, 8-week self-guided MBI was associated with significant reductions in stress and pregnancy distress among pregnant women who completed the intervention; however, attrition exceeded 50% [59]. In the study by Kelman et al [52] on web-based CBI versus web-based CBT for perinatal women and those planning pregnancy, retention at a 2-week follow-up was 62% for CBI versus 71% for CBT.

As the field of pre- and perinatal meditation training advances, questions are raised about the types of meditation training, their suitability, and expected outcomes. In addition, there are enduring questions about how best to engage pregnant women in internet-delivered mental health interventions. Initial findings regarding engagement and retention within studies suggest a need for attention to consumer-focused design in the developmental stage of the intervention protocols [60]. This pilot study is intended as a precursor to a larger study (the Mums’ Minds Matter [MMM] study), in which we aim to address some of these issues. The MMM study will involve a three-arm RCT comparing web-based mindfulness training, web-based loving-kindness and compassion training (LKCT), and web-based progressive muscle relaxation (PMR; active control) to improve positive mental health and psychological distress among pregnant women. Both experimental conditions in the study were developed with input from consumers (ie, women who had been pregnant) and were designed in line with the instructional design framework for MBIs proposed by Lippmann et al [54]. PMR was selected as an active control condition as it is considered safe for pregnant women, is associated with physical and psychological benefits in the perinatal period, and could be matched to the format and duration of the experimental conditions [61].

### Objectives

This study aims to pilot the overall MMM study design, including the recruitment, screening, randomization, assessment, and intervention methods to be used in the full-scale trial. In addition to piloting these methods, this study has 3 objectives: (1) to assess the feasibility of the full-scale trial by measuring recruitment to the trial and retention, engagement, and completion rates for each arm of the trial; (2) to explore the experiences of women in the study; and (3) to estimate the standard deviation values for each of the outcome measures to inform sample size calculations for the main trial.

## Methods

### Study Design

This is a randomized controlled trial (RCT) with 3 parallel groups: (1) mindfulness training, (2) LKCT, and (3) PMR and a repeated measure design. The trial is single blinded, with block randomization to have equal allocation of participants to groups stratified by parity. The trial is registered with the Australian New Zealand Clinical Trials Registry; the trial registration number of the study is 12620000672954p. This study was approved by the Joondalup Health Campus (JHC) Human Research Ethics Committee. An overview of the study design is shown in Figure 1.

**Figure 1 figure1:**
[figure not shown]
Participant flow through the study.

### Trial Site and Participating Centers

The MMM interventions are all web-based, and all data will be collected electronically. As the study will recruit women receiving antenatal care at JHC, this health campus is considered the physical trial site.

### Participants

#### Eligibility Criteria

Eligible participants are pregnant women participating in the ORIGINS project (ORIGINS) and receiving antenatal care at a metropolitan health campus (JHC). ORIGINS is a longitudinal birth cohort study that recruits pregnant women and their partners from 12 weeks of gestational age and follows them and their child until 5 years postpartum. ORIGINS is open to any women who are birthing their baby at JHC [62]. Participants considered for inclusion in the MMM study will be women (1) at 18 to 30 weeks of pregnancy; (2) aged ≥18 years; (3) able to read, write, and understand English; and (4) able to access the internet.

#### Sample Size

We aim to recruit 25 participants per treatment arm (75 participants in total). The recommended sample sizes per treatment arm for pilot trials are between 15 and 25 when the standardized effect sizes for outcomes in the main trial are expected to be medium (0.5) to small (0.2) [63].

### Recruitment

Participants will be recruited at or following their first antenatal assessment for ORIGINS. Participants will receive recruitment materials (a recruitment video and website link) via email and/or text message. Interested participants will be directed to the study website to complete electronic consent forms and web-based screening measures via REDCap (Vanderbilt University). In addition to assessing eligibility criteria and parity (for stratification), the screening assessment will include the Edinburgh Postnatal Depression Scale (EPDS). This is a valid tool for detecting symptoms of depression during pregnancy and postnatally [64]. Participants scoring above the thresholds for the risk of depression (total score ≥13) or reporting thoughts of self-harm (score of 1-3 on item 10) will receive a phone call from a registered psychologist to discuss referral to more targeted support services. They will not be excluded from participation in the study.

### Randomization, Allocation, and Masking of the Intervention Conditions

Following screening, eligible participants will be asked to complete a web-based assessment battery comprising the outcome measures for the main trial. Upon completion of this assessment battery, the REDCap randomization module will be used to randomize participants to 1 of the 3 conditions. Randomization will be stratified by parity (nulliparous or not). The research assistant (RA) will be notified by email when a participant has been randomized. Although participants will not be blinded to the intervention condition, the RA will code participants’ condition allocation in the database so that the data analyst is blind to allocation. Minimal sufficient identifying data will be used to link MMM participant IDs to participant IDs in the ORIGINS study. This will be used to obtain the ORIGINS study data on participants’ sociodemographic and birth outcome data.

### Participant Procedure

Once a participant has been randomized, the RA will add the participant to their allocated intervention condition in Teachable, the web-based system used to deliver the programs. Participants will then receive an automated email from Teachable prompting them to create a password. Participants will also receive a phone call from the RA to confirm that they have successfully logged in to the program and to answer any participant questions. Participants will be asked to nominate a start date for the program within the next week.

Participants will access their allocated condition within the MMM program either on a computer (via the Teachable website) or on a smart device via the Teachable app. On the basis of their nominated start date, participants will receive an automated weekly text message with a link to the weekly outcome measures. These measures involve self-reports of stress, affect, and emotion regulation and are also designed to prompt self-reflection. There are also questions about daily practice, intentions to continue practice, and barriers and facilitators to practice. Participants who indicate that they do not intend to continue practice in the next week will be asked if they wish to opt out of the program. Participants choosing to opt out will be directed to a survey, which will ask them about the reasons for opting out of the program and request program feedback. At the conclusion of the 8-week intervention period, participants will be emailed a link to the t1 (posttest) assessment battery. Participants will be emailed again with a link to the t2 (follow-up) assessment battery 3 months after giving birth.

### Interventions

All intervention conditions will be delivered on the web using the Teachable platform. The program is structured so that each day of the intervention is delivered as a separate *lesson*. The same intervention structure will be used for each condition: 8 weeks, with 1 formal practice (audio recording) to be practiced daily each week. Participants will also receive text instructions for 1 informal practice each week, which they are encouraged to practice as often as feasible. The informal practices are designed to support participants to integrate skills and learning into their daily activities.

Both the mindfulness training and LKCT interventions were developed following a two-step process. First, we conducted a scoping review of the literature to determine key components of MBIs and CBIs administered during the perinatal period. In addition to extracting data regarding intervention characteristics (eg, weekly themes, duration, mode of delivery, home practice), we also extracted data regarding specific considerations for delivering meditation-based interventions during pregnancy. These data were used to develop a draft intervention protocol for the mindfulness training and LKCT conditions. The protocol was developed by AF and AO, who have masters-level training in clinical psychology and are both certified teachers of MBIs and CBIs. The PMR condition was based on exercises described by Jacobson [65] and adapted for pregnancy by excluding muscle tension in the abdominal area.

The intervention protocol was also informed by prior theoretical and empirical work describing the proposed mechanisms by which mindfulness and loving-kindness and compassion training impacts positive mental health and distress. For example, dismantling studies have supported the theory that acceptance is a necessary component for MBIs to improve positive emotions [66], whereas perspectives and empirical data on loving-kindness and compassion meditation highlight the central role of self-soothing, caring motivations, and socioaffective processes (eg, directing loving thoughts toward another) [37,67-69]. Finally, the structure of the intervention conditions was informed by the instructional design model for internet-based MBIs proposed by Lippmann et al [54]. These include the use of formal and informal practices, provision of educational and supportive material, and the use of reminders (via text message) at least once a week. The core themes and practices for each condition are described in Table 1. Further information on the formal practices can be found in Multimedia Appendix 1.

**Table 1 table1:** Outline of key themes and practices for each condition.

Components	Mindfulness training	Loving-kindness and compassion training	Progressive Muscle Relaxation
Themes	Nonjudgmental awareness of present-moment experiences (thoughts, feelings, and sensations); acceptance of present-moment experiences (thoughts, feelings, and sensations); using the breath as an anchor for attention; and how mindfulness can support perinatal health	Friendliness toward self; loving-kindness toward self, baby, and others; self-compassion; responding to difficulties with kindness and compassion; and how loving-kindness and compassion can support perinatal health	Relaxation and how relaxation can support perinatal health
Formal practices	Body scan, breath-focused meditation, walking meditation, and mountain meditation	Compassionate check-in, compassionate body scan, soothing image practice, loving-kindness practice, and responding to emotions with compassion	Progressive muscle relaxation exercise
Informal practice	Mindfulness of daily activities (chores, showering, and waking up), mindful communication, mindful walking in nature, and 3-min breathing space	Body softening practice, micromoments of soothing, on-the-spot loving kindness practice, and savoring practice	Informal relaxation applied in different contexts (eg, going to bed, driving, waking up)

Consumer testing and input for the mindfulness training and LKCT protocols were sought from a group of 16 women (8 per condition) who had a recent experience of pregnancy and had given birth in the past 5 years. Women accessed the meditation recordings and associated content on the web via the Teachable platform over the course of 4 weeks. They were asked to practice formal and informal practices and provide feedback on each practice using a web-based questionnaire. Reponses were collated and discussed in a series of focus groups (2 per treatment condition) where participants described their motivations and experiences with the intervention protocol and suggested revisions to the content and structure. For example, based on participant feedback, the practices in weeks 1 and 2 for each condition were changed from 15 min to 7 min and 10 min, respectively. Recordings were also amended to include background music. LKCT meditation practices were also slightly modified with regard to the terms used (eg, removal of the word *suffering*). The resulting intervention protocols involved daily practice of 7 min in week 1, 10 min in week 2, and 15 min in weeks 3 to 8, coupled with psychoeducation and 1 informal practice per week.

### Data Collection

#### Study Outcomes

We will assess several metrics to determine the feasibility of the study across the following domains: recruitment, randomization, retention, and adherence (Table 2). To assess the feasibility of the assessment battery and calculate standard deviations on the measures, the main outcome measures for the full-scale RCT will be used (Table 3). Postintervention interviews will be conducted with a randomly selected sample of participants (n=approximately 15 in each condition) to gather further data on engagement with practice, reasons for attrition, satisfaction with the program, enjoyment and value of the program, and barriers and facilitators to engagement. Participants will be invited to partake in a semistructured interview by telephone, videoconference, or at the JHC clinic. Table 4 shows the Standard Protocol Items Recommendations for Interventional Trials (SPIRIT) schedule of enrollment, interventions, and assessment.

**Table 2 table2:** Summary of outcomes and metrics for pilot study.

Outcome	Metrics
Recruitment	Number of participants screened per week Number of participants enrolled per week Proportion of recruited ORIGINS participants electing to enroll
Randomization	Proportion of eligible participants who access the web-based intervention following randomization Proportion of eligible participants who complete at least one session (one day) of the web-based intervention
Retention	Proportion of participants that complete t0 (baseline) measures after commencing them Condition-specific completion rates following randomization (completion defined as ≥50% of modules accessed at least once) Proportion of participants commencing baseline measures that complete time 1 (posttest) and time 2 (follow-up) measures
Adherence	Self-reported completion of practice Lesson completions in Teachable program
Acceptability	Proportion of participant opt-outs from each intervention condition Proportion of participant withdrawals from the study Self-reported intervention and study satisfaction

**Table 3 table3:** Summary of outcomes and measures for a full-scale randomized controlled trial.

Outcomes		Measures

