### Analytic Plan

#### Quantitative Analysis

The baseline characteristics of the participants will be reported to describe the sample. Descriptive statistics will be used to summarize the quantitative data collected for each feasibility domain. Feasibility metrics will address the ADePT (*a process for decision making after pilot and feasibility trials*) framework [79]. This feasibility framework has been incorporated as part of a phased approach to the development and evaluation of the intervention. Feasibility assessment will use both quantitative feasibility data and qualitative data derived from the postprogram interviews. According to the ADePT framework, the progression criteria to move from a pilot to full-scale trial are divided into 3 categories: green, red, and amber (Table 5). Although the purpose of the study is not hypothesis testing, we will calculate the differences between the experimental groups and the control condition for primary and secondary outcomes.

**Table 5 table5:** Decision-making criteria for full-scale randomized controlled trial, adapted from the “a process for decision making after pilot and feasibility trials” framework.

Outcome	Metrics
Green (proceed to full-scale RCT^a^ without refinement)	≥50% of eligible participants consent to the pilot trial ≥70% of consented participants commence each intervention arm ≥50% of consented participants complete all intervention sessions in each intervention arm Program satisfaction ratings and postprogram interventions demonstrate high satisfaction and acceptability of the program for ≥50% participants
Red (do not proceed to full-scale RCT)	<30% of eligible participants consent to the pilot trial <20% of consented participants commence each intervention arm Program satisfaction ratings and postprogram interventions demonstrate low satisfaction or lack of acceptability of the program for ≥50% participants
Amber (consider proceeding to full-scale trial only after protocols have been refined)	Neither red nor green criteria were met. Findings from qualitative and quantitative data will be used to determine whether a full-scale RCT should proceed with revisions

^a^RCT: randomized controlled trial.

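### Table 5 can return Green with no threshold for completing the t1 or t2 measures, and the Table 2 retention metric counts women who were never randomised

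*Protocol article*

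**What the plan says.** **Objective.** Objectives states that feasibility of the full-scale trial will be assessed "by measuring recruitment to the trial and retention, engagement, and completion rates for each arm of the trial".

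**Progression rule.** Table 5 (Quantitative Analysis) opens with the row "Green (proceed to full-scale RCT", without refinement. It has four conditions: at least 50% of eligible women consent, at least 70% of consented women commence each arm, at least 50% complete all sessions in each arm, and at least 50% show high satisfaction and acceptability. Red uses consent (below 30%), commencement (below 20%) and low satisfaction. Amber applies only when neither Red nor Green is met.

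**Retention metrics.** Table 2 (Study Outcomes) has three retention lines: completion of the baseline battery among those who start it, condition-specific programme completion after randomisation (counted as modules accessed), and "Proportion of participants commencing baseline measures that complete time 1 (posttest) and time 2 (follow-up) measures".

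**Sequence.** Randomization, Allocation, and Masking says: "Upon completion of this assessment battery, the REDCap randomization module will be used to randomize participants to 1 of the 3 conditions".

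**Background.** The section on web-based interventions cites a trial of an 8-week web-based mindfulness programme in pregnancy with attrition above 50%, and a web-based compassion trial in which "retention at a 2-week follow-up was 62% for CBI versus 71% for CBT".

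**The concern.** The main trial's primary outcome is the Mental Health Continuum–Short Form, collected at t0, t1 and t2 (Tables 3 and 4). Whether women will return it after 8 weeks, and again 3 months after birth through an emailed link, is one of the main things a pilot should settle. Table 5 does not ask. Session completion measures adherence, and a woman can finish the sessions without answering the posttest. Because Amber is reached only when Green fails, poor outcome retention cannot move a pilot out of Green once the four listed conditions are met.

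The second issue is separate. The outcome-retention line in Table 2 starts counting before randomisation. Women who abandon the baseline battery are never allocated, yet they count as lost. The result mixes pre- and post-randomisation loss, and it cannot be given for each arm as Objective 1 requires. The one retention line that is post-randomisation and by condition counts modules accessed, not outcome data.

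**Working it through.** **Inputs.** Sample Size: "We aim to recruit 25 participants per treatment arm (75 participants in total". Study Design: equal allocation to three arms. Table 5: the Green thresholds above. Table 2: the retention line. No baseline-completion rate and no t1 or t2 response rate is given, so ranges below are assumptions.

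**1. The plan's own figure.** 3 × 25 = 75, which reproduces.

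**2. Table 5 against the outcome data.** None of the four Green or three Red conditions refers to t1 or t2 completion. Satisfaction might constrain t1 indirectly if rated then, but Table 5 states neither its time point nor its denominator, and Table 4 has no satisfaction row.

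**3. Smallest Green pilot** (taking 25 consented and randomised per arm).
- Commence: 0.70 × 25 = 17.5, so 18.
- Complete all sessions: 0.50 × 25 = 12.5, so 13.
- If only all-session completers return t1: 3 × 13 = 39, and 39/75 = 52%.
- t2, if a share *c* of those 39 also responds, is 0.52 × *c*:

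| *c* (assumed) | t2 data as share of 75 |
|---|---|
| 90% | 46.8% |
| 80% | 41.6% |
| 70% | 36.4% |
| 62% | 32.2% |

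Losing two of the 39 is enough to fall below half: 37/75 = 49.3%.

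**4. Effect on Objective 3 (SD estimation).** The 95% interval for a pooled SD, as a multiple of the estimate, runs from √(df/χ²₀.₉₇₅) to √(df/χ²₀.₀₂₅), with df = n − 3 and normality assumed.
- n = 75 (df 72): 0.86 to 1.20.
- n = 39 (df 36): 0.81 to 1.30.

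This concerns posttest and follow-up SDs. Baseline SDs are unaffected.

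**5. The Table 2 denominator.** Let *b* be the share of baseline starters who finish and are randomised, and *r* the retention among the randomised. Table 2 reports *b* × *r*. With *r* = 70%:

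| *b* (assumed) | Table 2 figure |
|---|---|
| 95% | 66.5% |
| 90% | 63% |
| 80% | 56% |
| 70% | 49% |

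The shift is always downward.

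**6. Can *r* be recovered?** Overall, yes. Suppose 88 start, 75 are randomised and 53 complete t1. Then 53/88 = 60.2%, 75/88 = 85.2%, and 60.2/85.2 = 70.7% = 53/75. By arm, no: the women who stop before allocation belong to no arm, so the metric has no arm-specific denominator.

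**7. How a threshold would behave at this size** (illustrative cut-offs, binomial, equal true retention in all arms).
- Green at 70% in every arm, true retention 80%: Pr(X ≥ 18 of 25) = 0.891, and 0.891³ = 0.71.
- Red below 50% in any arm, true retention 60%: Pr(X ≤ 12 of 25) = 0.154, and 1 − (1 − 0.154)³ = 0.39.
- The same cut-offs on all 75: Pr(X ≥ 53) = 0.98 at 80%, and Pr(X ≤ 37) = 0.04 at 60%.

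**The case against.** The best defence is that retention is not neglected. Table 2 prespecifies and measures it, the interviews explore reasons for attrition, and Quantitative Analysis says feasibility will draw on both quantitative and qualitative data. The per-arm session-completion criterion addresses programme dropout, which may be what the cited attrition above 50% refers to; the article does not say whether that figure means dropout or missing outcome data. On this view only a numeric cut-off is missing, in a pilot that tests no hypothesis. This stands as to measurement and lowers the severity. It does not answer the point that Table 5, as written, gives its verdict without using the measurement.

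On the denominator, the defence is largely right for the overall rate, which can be recovered by dividing one Table 2 line by the other. Objective 1 also signals an intention to report by arm. What remains is that the metric as defined cannot deliver it.

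The defence is also right that a strict threshold would be hazardous here. An any-arm Red rule would often stop a programme with tolerable retention, as step 7 shows.

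**Conclusion.** The point holds as a should-fix. Table 5 can clear the full trial without refinement at t1 retention of about 52% and t2 retention below half. That rests on the minimum Green counts, on only all-session completers returning t1, and on a small further loss by t2. Separately, the Table 2 metric understates retention among the randomised by the factor *b* and cannot be split by arm as written.

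Four stronger readings are tempting, and the documents do not support them.
- *The denominator helps conceal attrition or produce Green.* It can only lower the reported rate, and it plays no part in Table 5.
- *Green is compatible with no t1 data at all.* This is a logical floor only. It would need at least half of each arm to finish all sessions and at least half of participants to be highly satisfied while nobody answers the posttest.
- *The pilot will lose most of its outcome data.* Nothing forecasts this; the rule merely permits it.
- *The understated rate will distort the main-trial sample size.* The article says SD values will inform that calculation. It nowhere says this retention rate will.

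**What to change.** **Table 5.** Add a progression criterion on completion of the Mental Health Continuum–Short Form at t1 among women randomised, and report t2 completion in the same way. The sponsor should fix the thresholds before enrolment and allow for the imprecision of 25 per arm. One workable form is a cut-off on all randomised women, with by-arm rates reported beside it and low retention leading to Amber rather than to a Red triggered by any single arm. An overall cut-off is less sensitive to differential loss, which is why the by-arm rates should be shown.

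**Table 2.** Change the denominator of the t1/t2 line to women randomised, by arm, and give t1 and t2 separate lines. Keep completion of the baseline battery as the separate line it already is.

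**Cost.** One added criterion and one redefined metric, using data already due to be collected. Green becomes somewhat harder to reach.
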